## **5.6 Treatment Fidelity Plan**

### **5.6.1 Initial Training for Procedural Reliability**

[name] and [name] will train the PTs in both the Standard and the Standard-plus interventions. Knowledge of procedures will be tested by psychomotor skills observation. [name] and [name] will document that the PTs are “PRIMA” certified PTs and provide a certificate of completion after they demonstrate competence with the interventions. All PT-CTRC PTs are CPR certified and must maintain this certification throughout the study. As new PTs join the study, training will be conducted on an individualized basis following the same procedures.

### **5.6.2 Ensuring Ongoing Competency**

We will use a multi-faceted approach to ensure ongoing treatment fidelity. The approaches include direct observation of skills, mandatory monthly telephone calls with all treating PTs, periodic review of intervention data sheets, and face-to-face meetings with the intervention team at least once per year.

Direct Observation of Skills: Direct observation of the PTs as they perform the interventions will be conducted by [name] or a senior research physical therapist trained in the intervention. The evaluators will document their observations using a structured checklist that addresses data completeness, physical performance, qualitative observations, and verbal and nonverbal communication. In the Standard intervention the checklist will also document whether the participant completed 5 minutes of warm-up, 10-15 minutes of lower extremity strength training consisting of exercises that address at least 3 muscle groups, 30-40 minutes total of endurance training at an RPE of 10-13, and a 5 minute cool down. In the Standard-plus intervention the checklist will also document whether the participant completed 5 minutes of warm-up, 10-15 minutes of lower extremity strength training consisting of exercises that address at least 3 muscle groups, 15-20 minutes of endurance training at an RPE of 10-13, 15-20 minutes of timing and coordination training and a 5 minute cool down. There will be two observations per quarter for each intervention for new PTs and one observation for each intervention per quarter for PTs who have been with the study more than 6 months. If the total score on the checklist is less than 90% a remediation plan will be developed that will include refresher training to ensure adequate understanding of the protocol and follow-up observation visits.

Mandatory monthly check ins: [name] will conduct monthly check ins with the PTs delivering the intervention. The study coordinator be included in the phone call or email exchange and will document minutes and ongoing training where applicable. During these check ins, the PTs will be able to ask questions about the intervention delivery. The check ins will provide the PTs with an opportunity to brainstorm and problem solve with [name].

Periodic Review of Intervention data sheets: Intervention data sheets will be reviewed periodically to ensure the proper intervention is being delivered and that the intervention is being progressed over time. Review of intervention data sheets will occur at the completion of the on-site intervention. Initially, intervention data sheets from two of the first 5 participants in each intervention arm will be reviewed. Once the initial reviews are completed, subsequent reviews will occur quarterly (i.e. two participants in each intervention). If the documentation of the intervention and/or the progression of the intervention is inadequate, a remediation plan will be developed that will include refresher training to ensure adequate understanding of the protocol and follow-up observation visits.

Face-to-face meetings: [name] will visit the PT-CTRC semi-annually to meet with the PTs delivering the interventions. This will be a team building and problem solving visit emphasizing proper delivery of the intervention and discussing issues specific to the site.

## **5.7 Scheduling Intervention Visits**

There are several requirements for scheduling of intervention visits:

1. The first intervention visit should be scheduled 8-14 days after baseline testing is completed. Randomization is to be completed 1-2 business days before first intervention visit OR 14 days after baseline testing is completed.
2. The general schedule of visits includes 2 visits per week for 12 weeks for a total of 24 visits. The goal is to complete 24 visits. Missed visits because of illness, holidays, or vacations can be rescheduled in the following weeks; however, all visits must occur within a 14 week time period.
3. Intervention visits should never occur on two consecutive days.

## **5.8 Adherence Assessment**

Adherence to the intervention will be defined as the number of intervention sessions completed. Adherence to the exercise intervention (standard or standard-plus) will be tracked separately from the adherence to the behavioral intervention. The staff

delivering the intervention will track and record the attendance of the participant in the exercise intervention and the behavioral intervention on the adherence log form. At the completion of the intervention, the final total attendance will be entered into the database.

## **6    STUDY PROCEDURES**

## **6.1 Schedule of Evaluations**

| Assessment                                              | Phone Screen | Clinic Screen | Baseline | 12 week | 24 week | 36 week | Each intervention visit | As needed |
|---------------------------------------------------------|--------------|---------------|----------|---------|---------|---------|-------------------------|-----------|
| Phone Screen                            | X            |               |          |         |         |         |                         |           |
| Informed Consent Form                   |              | X             |          |         |         |         |                         |           |
| Demographics Questionnaire              |              | X             |          |         |         |         |                         |           |
| Physical Exam                           |              | X             |          |         |         |         |                         |           |
| Comorbidity Index                       |              | X             |          |         |         |         |                         |           |
| Anthropometric Measures                 |              | X             |          | X       | X       | X       |                         |           |
| Gait speed screen                       |              | X             |          |         |         |         |                         |           |
| Modified Mini-Mental State (3MS) Test   |              | X             |          |         |         |         |                         |           |
| Medical clearance to participate        |              | X             |          |         |         |         |                         |           |
| Fall history questionnaire              |              |               | X        | X       | X       | X       |                         |           |
| Gait Assessment Walkway                 |              |               | X        | X       | X       | X       |                         |           |
| Leg strength and power                  |              |               | X        | X       | X       | X       |                         |           |
| Six minute walk test                    |              |               | X        | X       | X       | X       |                         |           |
| Chair sit and reach                     |              |               | X        | X       | X       | X       |                         |           |
| Smoothness of walking                   |              |               | X        | X       | X       | X       |                         |           |
| Gait Efficiency                         |              |               | X        | X       | X       | X       |                         |           |
| Figure of 8                             |              |               | X        | X       | X       | X       |                         |           |
| Gait Efficacy Scale                     |              |               | X        | X       | X       | X       |                         |           |
| Late Life Function and Disability Index |              |               | X        | X       | X       | X       |                         |           |
| Life Space Assessment                   |              |               | X        | X       | X       | X       |                         |           |

|                                                                    |  |  |   |   |   |   |   |   |
|--------------------------------------------------------------------|--|--|---|---|---|---|---|---|
| Pitt Sleep Quality Index                           |  |  | X | X | X | X |   |   |
| Geriatric Depression Scale                         |  |  | X | X | X | X |   |   |
| Actigraph Diary                                    |  |  | X | X | X | X |   |   |
| Exercise adherence log                             |  |  |   |   |   |   | X |   |
| Adverse events                                     |  |  |   | X | X | X |   | X |
| Change in status                                   |  |  |   |   |   |   |   | X |
| Health status update                               |  |  |   |   |   |   |   | X |
| Medical clearance to return after illness or event |  |  |   |   |   |   |   | X |
| Protocol deviation                                 |  |  |   |   |   |   |   | X |

## **6.2 Description of Evaluations**

### **6.2.1 Screening (Phone and Clinic)**

Screening will be conducted in two phases, phone and clinic. Initial phone contact uses a structured questionnaire to identify inclusion and exclusion by self-report. Individuals who meet the criteria will be scheduled for an onsite examination (clinic screen) to identify additional potential exclusions.

#### Consenting Procedure

Prior to the phone screen we will obtain verbal consent. During the initial telephone call, potential participants will be informed of the nature of the screening questions. They will also be informed that their answers to the questions will be stored confidentially. Additionally, they will be reminded that participation in the telephone screening is voluntary. The participant's verbal consent will be noted on the telephone screening form. If the potential participant declines the telephone interview, the form will be destroyed.

Medical Clearance. Once the participant passes the phone screen, we will obtain the name and phone number of the participant's primary care physician so that we can obtain medical clearance for participation in the study. The physician's office will be contacted and the fax number obtained. We will fax the physician's office a letter and a form for medical clearance and ask that it be completed and returned to us by mail or fax. Medical clearance must be obtained prior to the clinic visit for screening and baseline testing.

Prior to performing any of the clinic screen measures, written informed consent will be obtained. During the clinic screen visit, the participant will be given the consent form to read. The consent form will then be reviewed in the presence of one of the study investigators. The investigator will then answer any questions that the participant may have about the study. The investigator will ask the participant several questions about the study to make sure they understand the study procedures. Finally the participant will be asked to sign the consent form. The signed consent form will be stored in the participant's research record in a locked file cabinet. The participant will be given a copy of the consent form for their records.

#### Clinic Screen

The clinic screen will include the following measures:

- Demographic questionnaire
- Physical Exam
- Comorbidity Index
- Anthropometric measurements
- Gait speed – 4 meter walk

- Modified Mini-Mental State (3MS) test

All screening measures will be completed prior to determining subject eligibility. Once all measures are collected, the values will be reviewed to determine eligibility. Participants will be informed at the clinic screen visit of their eligibility. Participants who are not eligible will terminate participation at the end of the clinic screen. Participants who are eligible will continue on with baseline testing. All screening tests must be measured within 14 days of randomization.

### 6.2.2 Baseline

Baseline assessment will occur immediately following the clinic screen and will include the following measures:

#### **Mobility Outcome (Primary Outcome):**

Gait Speed - The primary mobility outcome is gait speed. We selected gait speed as our primary outcome because of its strong psychometric properties, its significant association with morbidity and mortality, and the continuous nature of the variable. Gait speed is a reliable,(46, 47) valid, sensitive(11) and specific(48) measure that correlates with functional ability and balance confidence. Gait speed is strongly association with future disability, falls, hospitalization, nursing home admission and mortality.(1-5) Gait speed is a responsive measure that can assess change over time(11, 49) thus an improvement in gait speed is likely a good indicator of the effectiveness of an exercise program. In addition, gait speed was chosen by a panel of experts as the standardized assessment to measure locomotion for the Motor Function Domain of the NIH Toolbox.

Gait speed is assessed in usual walking with a computerized walkway. After explanation and demonstration, the participant completes a practice walk the length of the walkway to become accustomed to walking on the mat. Each walk is considered one pass. The subject then completes 6 passes on the walkway at their usual, self-selected walking speed. Gait speed will be averaged over the 4 passes. The test-retest reliability of gait speed measured using a computerized walkway by ICC is 0.98.(50) A higher speed is better.

#### **Outcomes representing components of the interventions (Secondary Outcomes):**

In order to assess the integrity of the intervention, we selected measures that represent the main components of the intervention (i.e. strength, endurance, flexibility, and timing and coordination) as our secondary outcomes. Measures representing the underlying components of the interventions are:

Lower Extremity Strength and Power - Leg strength will be measured by determining the 1 repetition maximum (1RM) for each leg individually using a Keiser A420 electronic pneumatic leg press machine. We will follow the protocol previously described by Callahan et al, 2007.(51) The maximum value observed on the A420 graphical display of either side will be recorded as the peak leg strength. Leg press power will also be

measured using the Keiser A420 leg press machine. Leg press power will be measured as the peak power graphically recorded when the individual performs a single leg press repetition pushing out as quickly as possible at 40% and 70% of 1RM. Five repetitions will be recorded for each leg at each resistance. The highest recorded power of all repetitions (either side, either resistance) will be recorded as leg press power.

Six Minute Walk Test (6MWT) - The Six Minute Walk Test (6MWT) of distance walked (meters) in six minutes, including time for rest as needed,(52) will be used to determine the impact of the exercise interventions on endurance. The 6MWT has been used to describe and monitor endurance capacity.(52) The 6MWT has established psychometric properties, test-retest reliability (Pearson  $r=.95$ ) in older adults,(48, 53) construct validity for graded exercise test and functional classification.(54) We chose the 6MWT because it is responsive to change,(55) widely used, and included in the NIH, PROMIS project to establish measures for clinical assessment. Greater distance covered during six minutes is better.

Chair Sit-and-Reach Test - The Chair Sit-and-Reach Test, a measure of hamstring flexibility, will be used as the main measure of flexibility.(56) Subjects sit on the edge of a chair with their preferred leg extended and the other leg bent with the foot flat on the floor. Subjects bend forward at the hips, keeping the spine as straight as possible. The distance reached in relation to the foot is recorded in cm. The Chair Sit-and Reach test was selected as the measure of flexibility because it does not require the older adult to sit on the floor, which may be difficult for some. The test has established psychometric properties of test-retest reliability (ICC=0.92-0.96) and criterion validity with comparison to the sit-and-reach test ( $r=0.74$ ). Values can be positive or negative with positive numbers indicating greater flexibility.

Smoothness of walking – Smoothness of Walking is an integrated measure of motor control of walking,(57, 58) and is assessed during usual over ground walking. Linear acceleration of the body is measured along three axes (vertical, anterior-posterior and medial-lateral) using a tri-axial accelerometer attached to the skin over the L3 segment of the lumbar spine. Trunk accelerations are sampled at 200 Hz and are used to calculate the harmonic ratio following the methodology of Menz.(57) The harmonic ratio (HR) is derived in the vertical, medial-lateral and anterior-posterior directions. Higher HRs are better.

Gait variability – Gait variability, defined as fluctuations in gait characteristics from one step to the next,(59) is an important indicator of impaired mobility in older adults and will serve as a second indicator of timing and coordination.(60) Gait variability is quantified using established measures of temporal and spatial gait characteristics including stance time, step length, and step width. Variability will be calculated as the standard deviation of the set of steps recorded over 4 passes on the GaitMat (described above). Approximately 32 steps will be collected from 4 passes on the GaitMat which will be more than adequate to achieve a stable measure of gait variability. Our prior work has shown that 20 steps are sufficient to achieve a reliability of 0.75 and 30 are sufficient for 0.80.(61) In general, lower variability is better although there are exceptions.(60, 62)

Gait Efficiency - We will use the energy cost of walking as our indicator of gait efficiency. The energy cost of walking reflects the energy used for all bodily actions

during walking.(63) Subjects walk on a treadmill at a self-selected pace while oxygen consumption data is collected using open circuit spirometry and analysis of expired gases with a VO2000 portable metabolic measurement system, Medgraphics®, Minneapolis, MN. All subjects are familiarized with treadmill walking until comfortable walking on the treadmill, prior to the baseline measurement. The mean rate of oxygen and carbon dioxide consumption is determined over three minutes after reaching steady state.(63, 64) The energy cost of walking reported in ml/kg/m, represents an estimate of energy expenditure per unit of gait speed,(65-67) and relates to metabolic equivalents (METS). It is time independent, repeatable, reflects the physiological cost of gait,(63, 64) is little influenced by fitness,(63) and can be compared across individuals and over time, regardless of changes in gait speed.(63, 65) Lower cost is better.

### **Activity Outcomes (Tertiary Outcomes):**

Using the World Health Organization's International Classification of Functioning, Disability and Health (ICF)(68) model to inform our selection of tertiary outcomes for this study, we will evaluate measures of activity (execution of a physical task).

### **Activity levels will be assessed with:**

The Late Life Function and Disability Instrument (LLFDI-F).(14, 69) The LLFDI-F is our main activity outcome. The LLFDI-F is a self-report measure for assessing physical function in older adults with acute or chronic problems, and designed to be more sensitive to change than similar measures. The LLFDI-F has 32 items in three dimensions, basic lower extremity (BLE), advance lower extremity (ALE) and upper extremity (UE). We've selected the LLFDI-F because 1) it includes a wide variety of life tasks in various social areas thus extending beyond the traditional focus of just activities of daily living, 2) the scale was designed with sufficient breadth of items and increments of rating in order to minimize ceiling and floor effects and maximize the scale's ability to detect change over time, and 3) it is a continuous outcome which gives us greater power than a dichotomous outcome to detect change over time. We will focus our analyses on the LLFDI-F dimension scores (i.e. BLE function, ALE function, UE function). The LLFDI-F has established known groups validity and the test-retest reliability is extremely high for the function component (ICCs range from 0.91-0.98 for the dimensions). Scores range from 0-100; higher scores represent less difficulty.

### **Participation Outcomes (Tertiary):**

Using the ICF(68) model to inform our selection of disability outcomes for this study, we will evaluate measures of participation (involvement in life situations). Participation levels will be assessed with:

The Late Life Function and Disability Instrument (LLFDI-D).(69) The LLFDI-D is our main participation outcome. The LLFDI-D is a self-report measure for assessing disability in older adults with acute or chronic problems, and designed to be more sensitive to change than similar measures. The LLFDI-D component has 16 items representing two dimensions, frequency of performance and limitation in performance of life tasks. We will focus our analyses on the LLFDI-D dimension scores (i.e. disability frequency and disability limitation). We will also examine the disability domain scores

(social role, personal role, instrumental role and management role) since they may provide insight into the impact of the disability on frequency of performance and perceived limitations.(69) The LLFDI-D scales have established known groups validity and the test-retest reliability is moderate to high (ICCs range from 0.68 to 0.82). Scores range from 0-100; higher scores represent less disability.

The Actigraph Accelerometer will be used to assess the participants' usual daily physical activity. The ActiGraph is often used in physical activity research and has recently been shown to be more reliable than other devices.(70) Accelerometers are electronic sensors that measure the quantity and intensity of ambulatory movement.(71) Due to the small size and weight of the monitor, the participant is not expected to experience a disruption in their gait or balance. The Actigraph Accelerometer will be worn on the waist during waking hours for 7 consecutive days, and the participants will be instructed to remove the monitor only for sleeping, during imaging studies, and or during swimming and bathing activities. For pre-intervention physical activity assessment the subject will be given the accelerometer during the baseline assessment. They will be asked to return the accelerometer during their first intervention visit. For post-intervention testing, the subject will receive the accelerometer during the last intervention visit and will be asked to return it during the post-intervention assessment. For the 24 and 36 week follow-ups the participant will be given the accelerometer during their visit and they will be asked to return it by mail in a postage paid envelope. We used the same methodology (returning by mail) in a past study of 120 older adults and received accelerometers back from > 95% of the subjects. The continuous data that are available through actigraphy provide many possible measures for analysis. We focus on 1) total activity counts, 2) percentage of time spent in sedentary activity and 3) number of bouts of moderate intensity activity as our outcomes.

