**Interventions and Duration.** Intervention sessions are twice weekly for 12 weeks supervised by a physical therapist. All sessions last about 50-65 minutes and include a warm-up, 40-55 minutes of exercise, and a cool down period. Both intervention groups will also receive physical activity behavioral change intervention. The Standard Intervention includes a brief warm-up period, lower extremity strength training, endurance training, and a brief cool down period. The Standard-Plus Task Specific Timing and Coordination Intervention or Standard-Plus intervention includes all components of the Standard Intervention plus task specific timing and coordination training. The total intervention time will be equal between the two intervention groups.

**Sample Size and Population.** The target sample is community-dwelling older adults who walk faster than 0.60 m/s and slower than the desired gait speed of 1.2 m/s. We plan to enroll approximately 124 subjects who walk slowly (i.e. gait speed  $> 0.60$  and  $< 1.0$  m/s) and approximately 124 faster walkers (i.e. gait speed  $\geq 1.0$  and  $< 1.20$  m/s) for a total of 248 subjects. Within each baseline gait speed stratum we plan to randomize individuals to each of the treatment arms so that the gait speed strata are equally represented in each of the arms. Persons who are unable to participate in testing, have medical conditions which would make testing or participation in an exercise program unsafe, or who have plans to permanently leave the area during the study are excluded.

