## **5.2 Blinding and Study Staff**

Given the nature of the interventions being tested in this study, it will not be possible to blind the participants or the PT providing the interventions. To minimize “contamination” of the interventions, participants receiving different interventions will not be scheduled during the same time at the PT-CTRC. Study staff involved in the randomization or intervention will not perform follow-up data collection. Study staff performing the follow-up assessments will be blinded to treatment assignments and will be asked not to seek this information when in contact with the participants. Participants will be asked not to discuss their treatment experience during study visits. Only a small number of staff members and members of the DSMB will see group-specific study results.

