## 9. **INTERVENTION DISCONTINUATION**

Certain events may result in a temporary interruption or early discontinuation of the trial assessments and interventions or components of these assessments and interventions.

Please refer to the appropriate MOP chapter(s) for specific instructions on stopping criteria during screening, assessment, interventions, and follow-up assessments.

After such events occur, a participant may resume the trial intervention when the study physician and the primary care provider agree that it is appropriate. For mild problems that require temporary cessation of the intervention, the PI in consultation with the study physician and the participant, may agree to reintroduce the participant to the study intervention.

At any time, the DSMB may recommend discontinuation of any component of the intervention or intervention group of the study for any of the following reasons:

1. Compelling evidence from this or any other study of an adverse effect of the study intervention(s) that is sufficient to override the potential benefit of the interventions to the target population
2. Compelling evidence from this or any other study of a significant beneficial effect of the study intervention(s), such that it is continued denial to other study group(s) would be unethical
3. A very low probability of addressing the study goals within a feasible timeframe.

The participants' participation in this research study is completely voluntary. The participant may withdraw, at any time, their consent for participation in this research study. Any identifiable research information recorded for, or resulting from, their participation in this research study prior to the date that they formally withdrew their consent may continue to be used and disclosed by the investigators. To formally withdraw consent for participation in this research study the participant should provide a written and dated notice of this decision to the principal investigator of this research study. If the participant withdraws from the intervention, study staff will ask permission to continue to follow the participant for follow-up assessment. If participation is discontinued for medical reasons and the participant is unable to complete the performance-based testing, all attempts will be made to obtain the self-reported outcomes.

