## **11 DATA COLLECTION AND QUALITY ASSURANCE**

### **11.1 Data Collection Forms**

Data collection will consist of a combination of paper forms and direct data entry. Data collected on paper forms will be entered into the electronic database by the research staff. A complete set of paper forms will be available at all times to be used if the database is temporarily unavailable. Please see the Manual of Procedures for a copy of all data entry forms.

Screening and baseline data collection, which will occur prior to randomization, will be conducted by research staff trained in the outcomes and may include the study coordinator if necessary. Outcome assessments at 12, 24 and 36 weeks will only be conducted by research staff trained in the outcomes and who are blinded to the intervention group assignment.

Participants' confidentiality will be protected in the data collection process. All study personnel are certified in Research Practice Fundamentals, Human Subjects Research Module. Consent forms and paper data collection forms will be stored in locked file cabinets. All computers are password protected. The database will be web-based and accessible with a username and password. Only authorized team members will have access to personal information needed for tracking and informed consent.

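### The 12-week activity monitor is issued only at the last training session, so people who stop training but stay in follow-up have no stated route to one

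*Supplement*

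**What the plan says.** The accelerometer paragraph in protocol section 6.2.2 (Participation Outcomes) sets out the logistics wave by wave. At 12 weeks: "For post-intervention testing, the subject will receive the accelerometer during the last intervention visit", and the participant "will be asked to return it during the post-intervention assessment". At the later waves: "For the 24 and 36 week follow-ups the participant will be given the accelerometer during their visit", with return in a prepaid envelope. The baseline monitor is also given at an assessment.

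Section 9 covers people who stop training: "If the participant withdraws from the intervention, study staff will ask permission to continue to follow the participant for follow-up assessment".

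Section 1.2 includes accelerometer-measured activity among the outcomes expected to improve more with standard-plus at 12 weeks. Section 6.2.3 lists the Actigraph for 12, 24 and 36 weeks without reference to training attendance. The final analysis plan is by intention to treat with multiple imputation. Its summary of changes adds that the actigraphy variables were imputed separately from the other outcomes.

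**The concern.** At three of the four waves a participant gets the monitor by attending an assessment. At 12 weeks the participant gets it by attending a training session, and specifically the last one. Someone who stops training in week 5 and agrees to remain in follow-up can attend the 12-week assessment and have gait speed, the six-minute walk and the questionnaires measured. The text gives that person no way to have worn a monitor.

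The intention-to-treat comparison of 12-week activity would then rest on observed values almost entirely from people who reached the end of training. Reaching the end of training happens after randomization and is plausibly related to activity level. If stopping differs between arms, so does the selection.

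**Working it through.** **1. The four waves side by side (section 6.2.2)**

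| Wave | Monitor issued at | Returned | Issue depends on training attendance |
|---|---|---|---|
| Baseline | baseline assessment | first training visit | no |
| 12 weeks | last training visit | 12-week assessment | yes |
| 24 and 36 weeks | assessment visit | by post | no |

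Set against section 9, the 12-week row leaves people who have stopped training but are still followed without a described route. The documents shown contain no fallback and no statement that such people are excluded from the measure.

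**2. What the plan's own figures cover**

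Section 10.5 expects 10, 15 and 20% dropout and 55, 52 and 49 completers. With 62 per arm per stratum (section 10.5.1):

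- 62 × 0.90 = 55.8
- 62 × 0.85 = 52.7
- 62 × 0.80 = 49.6

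Rounded down, these reproduce the stated counts. They describe loss from the study. No rate is given for stopping training while staying in follow-up, and no SD is given for any actigraphy outcome. The next steps therefore use assumed ranges.

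**3. How many people**

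Assume 5 to 15% of each arm stop training but stay in follow-up. With 124 per arm, 0.05 × 124 = 6.2 and 0.15 × 124 = 18.6, so about 6 to 19 per arm.

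**4. Possible bias before imputation**

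Let p be the share of an arm without a 12-week value because they stopped training, and d the amount, in SD of change, by which their mean change falls below that of people who finished. Using observed values only, each arm's mean change is too high by p × d, so

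bias in the contrast = p₁d₁ − p₂d₂, which is (p₁ − p₂) × d when d is equal in both arms.

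- Low end: a 5-point difference in stopping and d = 0.3 gives 0.05 × 0.3 = 0.015 SD.
- High end: a 10-point difference and d = 0.8 gives 0.10 × 0.8 = 0.08 SD.
- Equal stopping rates and equal shortfalls give 0.

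**5. Precision**

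Detectable difference at 80% power, two-sided 0.05: (1.960 + 0.842) × √(2/n).

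| Missing | n per arm | Detectable difference (SD) |
|---|---|---|
| 0% | 124 | 0.356 |
| 10% | 111.6 | 0.375 |
| 20% | 99.2 | 0.398 |
| 30% | 86.8 | 0.425 |

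The loss of precision is modest. The worst assumed bias, 0.08 SD, is less than a quarter of the smallest detectable difference (0.08 / 0.356 = 0.22).

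**6. What imputation can and cannot do**

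People who stop training may have baseline values and, if they attend, 24- and 36-week values, since those monitors are issued at the visits. Imputation can use all of these. How 12-week activity relates to the other waves, however, would be estimated mainly from people who finished training. If that relation differs just after stopping, the imputed values carry the difference forward unseen.

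**The case against.** The protocol does not say that people who stop training are refused a monitor. Section 6.2.3 lists the measure for everyone, section 6.1 schedules the monitor diary at 12 weeks, and section 9 refers to a manual of procedures that is not shown and may hold a fallback. On this view section 6.2.2 only describes the usual case. That stands as far as it goes: the gap is in the stated route, and what happened in practice is unknown.

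The stakes are also limited. Daily activity is a tertiary outcome, the disability score is named as the main participation measure, and section 2.4 expects activity changes to be delayed. The final plan puts the large amount of missing actigraphy down to its not being required before randomization, with no mention of this hand-out. All of this is correct and keeps the point small. It does not remove it, because the 12-week comparison is still a stated hypothesis.

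A reader might go further and infer a breach of masking. Sessions are run by therapists ("Intervention sessions are twice weekly for 12 weeks supervised by a physical therapist"), of whom section 5.2 says "it will not be possible to blind the participants or the PT providing the interventions", while the same section states: "Study staff involved in the randomization or intervention will not perform follow-up data collection". The documents do not support that reading. They do not say who hands over the monitor. Handing over a self-worn recorder is not clearly data collection. The monitor comes back at a visit covered by section 11.1: "Outcome assessments at 12, 24 and 36 weeks will only be conducted by research staff trained in the outcomes and who are blinded".

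**Conclusion.** The point holds as a small, inexpensive improvement to one tertiary outcome at one time point. As written, issue of the 12-week monitor depends on training attendance, and people followed after stopping have no stated way to get one, so missing values would be linked to stopping. The primary outcome is not affected.

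The size cannot be derived from the documents. The 0.015 to 0.08 SD range rests on assumed stopping differences of 5 to 10 points and assumed shortfalls of 0.3 to 0.8 SD, and it gives imputation no credit.

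Two stronger readings should not be drawn. One is that intervention staff collect follow-up data, which the text does not show. The other is that imputation is powerless here: it has these participants' other waves to work with, although it leans on completers for the 12-week relation.

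**What to change.** Add a sentence to section 6.2.2. Every participant still in follow-up who has not received a monitor at a last intervention visit is given one at the 12-week assessment by masked assessment staff, or is posted one if not attending. It is worn for 7 days and returned by post, as at 24 and 36 weeks. Using this route for all participants is an acceptable option, since it would put every wave on the same footing, but it is not needed to close the gap.

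Report the number with usable 12-week actigraphy by arm and by whether training was completed. The final analysis plan is written in the past tense, so if the protocol change comes too late, this table and a statement of how people who stopped training received monitors are the useful remedy.

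The cost is slight: a few monitors not returned (the protocol cites more than 95% return by post in a past study of 120 older adults) and a wear week that falls just after the visit for the participants concerned.
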